## Abstract

**Background:**

Depression is common among people with diabetes, negatively affecting quality of life, treatment adherence and diabetes outcomes. In routine clinical care, diabetes patients have limited access to mental health services and depression therefore often remains untreated. Web-based therapy could potentially be an effective way to improve the reach of psychological care for diabetes patients, at relatively low costs. This study seeks to test the effectiveness of a web-based self-help depression programme for people with diabetes and co-morbid depression.

**Methods/Design:**

The effectiveness of a web-based self-help course for adults with diabetes with co-morbid depression will be tested in a randomised trial, using a wait-list controlled design. The intervention consists of an 8-week, moderated self-help course that is tailored to the needs of persons living with diabetes and is offered on an individual basis. Participants receive feedback on their homework assignments by e-mail from their coach. We aim to include 286 patients (143/143), as power analyses showed that this number is needed to detect an effect size of 0.35, with measurements at baseline, directly after completing the web-based intervention and at 1, 3, 4 and 6 months follow-up. Patients in the control condition are placed on a waiting list, and follow the course 12 weeks after randomisation.

Primary outcomes are depressive symptoms and diabetes-specific emotional distress. Secondary outcomes are satisfaction with the course, perceived health status, self-care behaviours, glycaemic control, and days in bed/absence from work. Questionnaires are administered via the Internet.

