### Outcome Assessment

#### Primary outcome measures

Primary outcome measure is the level of depression, measured by the online administered self-reported depression questionnaire Center for Epidemiological Studies Depression scale (CES-D) [26] at baseline, directly after completion of the course and at one and six months follow-up.

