#### Secondary outcome measures

Secondary outcome measures are: diabetes-specific emotional distress (PAID) [27], satisfaction with the course (self-developed questions), perceived health status (EQ5D and SF-12) [28], diabetes self-care behaviours (Amsterdam Diabetes Self Care Inventory), self-reported episodes of hypoglycaemia and glycaemic control (HbA_1c_) retrieved from the patients' medical charts via their physician.

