### Statistical Analyses

Analyses will be conducted according to the intention to treat principle. The data will be presented as categorical and continuous variables. Baseline characteristics will be compared for the intervention and waiting-list group using Student *t*-tests and χ^2^-tests. Analysis of variance (ANOVA) will be conducted with the CES-D (depression) as dependent variable, with two independent variables: time (within-subject) and group (between-subject). The same analysis will be performed with the PAID score (diabetes-related emotional distress) as dependent variable. Two analyses will be conducted. Firstly, the direct effect of the intervention will be determined. ANCOVA's will be performed in order to test whether both groups have different scores on the CES-D, at different points in time, with correction for potential confounders at baseline. Secondly, pre-post measurements will be conducted of all participants who have received the intervention. This will be analysed by means of a longitudinal regression analysis, which will be performed using Generalized Estimating Equations (GEE) [29], taking into account the correlational nature of repeated measures data within subjects, and securing minimal loss of patients due to incomplete data. Clinical effectiveness will be calculated by the amount of people who after completion of the course have a score on the CES-D of <16. The effect size will be calculated using Cohen's *d *[30].

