### Power calculation

The sample size was calculated using STATA, based on clinically relevant differences. Effect Sizes (ES) are calculated as the difference between the control group and the intervention group after the intervention, divided by the pooled standard deviation [30]. With 100/100 patients the study is powered to detect an ES of 0.35 (one-sided), with a power of 80% (α = 0.05). Based on a meta-analysis [23], we may expect an ES of 0.5 to 0.6 [18]. We anticipate 30% non-completion/exclusion, which will be compensated by over sampling (n = 286; 143 in each group).

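### The abstract names two primary outcomes and the methods name one, and no primary time is fixed for the CES-D

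*Protocol article*

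**What the plan says.** The Methods/Design paragraph of the abstract says: "Primary outcomes are depressive symptoms and diabetes-specific emotional distress". Its list of secondary outcomes, which follows, leaves distress out, so the abstract is consistent with itself.

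The body of the article says otherwise. Under Primary outcome measures: "Primary outcome measure is the level of depression, measured by the online administered self-reported depression questionnaire", that is, the CES-D alone. Under Secondary outcome measures, the PAID comes first: "Secondary outcome measures are: diabetes-specific emotional distress (PAID".

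The CES-D is to be measured "at baseline, directly after completion of the course and at one and six months follow-up". None of these times is singled out.

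Under Statistical Analyses, a time-by-group ANOVA is planned for the CES-D, and then: "The same analysis will be performed with the PAID score (diabetes-related emotional distress) as dependent variable". ANCOVAs are added for the CES-D only, to "test whether both groups have different scores on the CES-D, at different points in time".

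The Power calculation defines one effect size, the difference between arms after the intervention, and states: "With 100/100 patients the study is powered to detect an ES of 0.35 (one-sided), with a power of 80% (α = 0.05". According to the abstract and the Control group section, waiting-list patients are offered the course 12 weeks after randomisation.

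**The concern.** The set of primary outcomes decides what the trial may claim. With two published definitions, a result on the PAID alone is a primary success under the abstract and a secondary finding under the methods. Which definition applies could be settled after the data are seen.

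The unranked times add a second choice. A difference in the CES-D directly after the course and one only at a later visit could each be put forward as the primary result. The later of the listed times also differ in kind: by six months after the course, controls have been offered the intervention, so a between-arm contrast there no longer compares treated with untreated patients.

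The sample size allows for neither choice. It gives the whole 5% to a single test.

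**Working it through.** **1. The plan's own figure.** Inputs from the Power calculation: effect size 0.35 (SD = 1), one-sided α = 0.05, power 80%, 30% loss.

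- n per arm = 2 × (1.645 + 0.842)² / 0.35² = 100.9, rounded up to 101. The article states 100.
- Power with 100 per arm = Φ(0.35 × √(100/2) − 1.645) = Φ(0.830) = 79.7%.
- Loss: 100 / 0.70 = 142.9, so 143 per arm and 286 in total, as stated.
- A two-sided test would need 129 per arm and does not reproduce the figure.

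The stated size is therefore right for one outcome, one test and the full one-sided 5%.

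**2. Which times are randomised comparisons.** The course lasts 8 weeks, so the post-course assessment in the intervention arm falls at about week 8 and the one-month follow-up at about week 12. The Study Design section gives controls extra measurements at weeks 8 and 12, and they start the course after that. The six-month follow-up lies beyond it. At most two of the three listed times compare the intervention with an untreated control.

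**3. Error rate under each success rule.** Each test is taken at one-sided 0.05. The documents give no correlations, so these are assumptions. For two tests with correlation ρ, the chance of at least one false positive is 1 − P(Z₁ ≤ 1.645, Z₂ ≤ 1.645), with Z₁ and Z₂ bivariate normal.

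| Rule | Assumed ρ | False-positive rate |
|---|---|---|
| CES-D at one named time | – | 5.0% |
| CES-D or PAID, one time | 0 | 1 − 0.95² = 9.75% |
| CES-D or PAID, one time | 0.6 | 8.4% |
| CES-D at week 8 or week 12 | 0.7 | 8.0% |
| CES-D and PAID both required, one time | any | at most 5% |

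**4. Power under each rule**, with 100 evaluable per arm and a true effect of 0.35 on each outcome.

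- Both required: 0.797² = 63.5% if the outcomes are independent and 69.5% at ρ = 0.6. It reaches 79.7% only if they are perfectly correlated.
- Either sufficient, with α split to 0.025 each: power for each outcome is Φ(2.475 − 1.960) = 69.7%. Restoring 80% needs 2 × (1.960 + 0.842)² / 0.35² = 128.1, so 129 per arm. After loss this is 129 / 0.70 = 184.3, so 185 per arm and 370 in total.
- CES-D alone at one time: 79.7%, with 286 unchanged.

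**The case against.** The strongest reply is that the Methods section agrees with itself. The CES-D is primary, the PAID is secondary, and the sample size uses one effect size after the intervention. On this view the abstract is a slip, and multiplicity rules belong in an analysis plan that is not shown.

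Much of this stands. A condensed article need not set out an α split or a testing order, and their absence is not the point here. But an analysis plan cannot make two published statements of the primary outcome agree. Nor is the abstract plainly a slip: the abstract's Discussion and the Aims of the Trial both put distress beside depression as a target of the intervention.

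A reader might go further and infer that the 5% error rate is already lost, or that it rises to 13–15% (two outcomes at two times) or 17–19% (two outcomes at three times). The documents do not support this:

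- Inflation needs a rule that any one success counts, and no such rule is stated. That each test runs at 5% is itself inferred from the power calculation.
- The visit-by-visit ANCOVAs are planned for the CES-D only. The PAID gets the time-by-group ANOVA, so the four-test case is not the written plan.
- The six-test case counts a time at which controls have already been offered the course.

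A reader might also take the Primary outcome measures section to imply week 8. It lists three post-baseline times without ranking them. Week 8 follows only from the Power calculation, the 8-week course and the 8-week control measurement.

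**Conclusion.** The contradiction is certain, since it stands in the current text. It should be corrected because it concerns the primary outcome and the primary time is not fixed either.

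Its effect on the error rate is conditional and moderate: about 8–10% instead of 5% if either outcome at one time were enough, and about 8% if the CES-D at either of the two controlled times were enough. These figures assume each test at one-sided 0.05 and the correlations shown above. If both outcomes had to succeed, the error rate would be safe and the cost would fall on power. The sample size arithmetic is sound for a single primary test.

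**What to change.** Correct the abstract so that the CES-D is the sole primary outcome and the PAID is secondary, in line with the outcome sections and the Power calculation.

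Name one primary comparison: the between-arm difference in the CES-D at the post-course assessment, 8 weeks after randomisation and before controls start the course. Treat later times as supportive. Testing the PAID in fixed order after the CES-D is an option; plain secondary status is enough to remove the conflict.

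The change is wording only and leaves N = 286 as it is. The one cost is that a result on the PAID alone cannot be called a primary success. If the sponsor prefers to keep both outcomes primary, the success rule must be stated and the sample size recomputed. With either outcome sufficient and α split equally, that is 370 in total.

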**Discussion:**

The intervention being trialled is expected to help improve mood and reduce diabetes-specific emotional distress in diabetes patients with depression, with subsequent beneficial effects on diabetes self-care and glycaemic outcomes. When proven efficacious, the intervention could be disseminated to reach large groups of patients with diabetes and concurrent depressive symptoms.

**Trial registration:**

Current Controlled Trials ISRCTN24874457

## Background

Depression has been shown two times more prevalent among persons with type 1 or type 2 diabetes, compared to the general population [1]. Approximately 10% of the adult diabetes patient population suffers from major depressive disorder and another 10% from minor depression [1]. Data also suggest depression to be more persistent and recurrent in people with diabetes [2]. The costs of depression in diabetes are known to be high, not only in terms of suffering and reduced quality of life, but also in view of adverse medical outcomes (e.g. hyperglycaemia, diabetes complications), and societal and economic costs [3,4].

Based on evidence to date, psychological therapy (particularly cognitive behaviour therapy, CBT) is the treatment of choice for depression [5]. Only a few randomised controlled studies have been conducted to test the efficacy of anti-depressant therapies in persons with diabetes and co morbid depression [6-8].

Not surprisingly, depressive symptoms are likely to co-occur with high levels of diabetes-related emotional distress, as was confirmed in a recent international study [9]. While the optimal treatment for depression in diabetes is still being sought [10], there is good reason to assume that the efficacy of anti-depressant psychotherapy in diabetes can be enhanced when specific issues associated with the burden of living with this chronic disease are adequately addressed [11].

We recently conducted a study to test the effectiveness of a group Cognitive Behaviour Therapy (CBT) developed for patients in prolonged poor glycaemic control in a RCT, and found CBT to be most effective in patients who entered the study with elevated depression scores [12,13].

Offering diabetes-specific CBT to diabetes patients with depression should thus be able to improve psychological health, self-management behaviours and subsequent medical outcomes. However, access to psychological services is limited, both in primary and secondary routine diabetes care [10]. As pointed out by Glasgow et al [14], we need to consider ways to enhance dissemination of effective psychological interventions to persons with diabetes. In this context, we believe use of modern interactive technology, such as internet-based therapy should be considered. More so, since web-based psychological interventions have shown their utility across a range of problem areas and are likely to be cost-effective [15,16].

Web-based cognitive behaviour therapy (W-CBT) is recognized as an effective treatment option for depression and appeared to be well appreciated by patients [15,17-20]. In The Netherlands, we have seen an increase of internet-use in the past years, with about 83% of the households currently being "online" [21]. Internet-based therapy therefore has great potential to reach large groups of diabetes patients with co-morbid depression. To our knowledge, we would be the first to test the effectiveness of diabetes-specific on-line CBT for depression in persons with diabetes.

### Aims of the Trial

This study aims to test the effectiveness and appreciation of web-based cognitive behavioural therapy (W-CBT) for adult diabetes patients with depression in a randomized controlled trial. The experimental condition will be compared with a waiting-list control group. It is hypothesized, that W-CBT will be well-received by the participants and will appear to be significantly more effective than the control condition in reducing levels of depressed mood and diabetes-specific emotional distress, with subsequent positive effects on self-management behaviours and glycaemic control on the longer term.

## Methods/Design

### Study Design

We chose a two-arm randomised controlled trial (RCT) design; including 286 patients (143/143) (see power calculation). Measurements are scheduled at six points in time in the intervention group: at baseline, directly after completing the web-based intervention, and at 1, 3, 4 and 6 months follow-up. In the control group the same six measurements are scheduled with two additional measurements at 8 and 12 weeks after randomization (see flow chart, Figure 1).

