### Description of interventions

#### Intervention group

Patient enrolment will occur individually on a continuous basis, i.e. at any point in time during the study period. The number of included participants is not limited by physical capacity other than the number of coaches available. After inclusion criteria are met and the patient has returned the informed consent s/he will be randomly assigned to the intervention or the control group.

Patients assigned to the intervention group will receive a password per e-mail with which they can log in to the course. They will be instructed (and reminded per e-mail) to complete one session per week, during 8 consecutive weeks.

Coaches will send e-mails to participants as a way to encourage them to continue their efforts. Such reinforcement should help to keep patients on track with the course and lower the risk of drop-out. They also provide the participants with feedback on their homework assignments. It is clearly stated that coaches will not give advice on personal issues.

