#### Control group

Control group patients will receive an e-mail in which they are informed of the randomisation result, which means they will start the course after 12 weeks. To reduce the risk of loss of interest; participants placed on the waiting-list will automatically receive weekly protocollised e-mails with motivating, positive feedback to enforce them to remain involved in the study.

After eight weeks they are invited per e-mail to fill in the questionnaires again. Twelve weeks after randomization patients will undergo a second screening (using the CES-D-score ≥ 16 as a first screener for depression and additionally the CIDI interview) to confirm depression. If still eligible, the patient is invited to follow the course. Patients, who do not qualify, i.e. show (spontaneous) remission, are excluded at this point. Patients who developed suicidal ideation during the 12 weeks waiting period, are offered the opportunity to have an appointment with a diabetes psychologist of the VU University Medical Centre or a colleague nearby in case the distance from the participant's home to the VUMC should be problematic.

The effectiveness of the intervention is determined directly after completing the web-based intervention up till 6 months follow-up (see Consort flow chart in Figure 1).

If the depression has deteriorated at the end of the course, as indicated by the scores of the CES-D, a consultation with a diabetes psychologist at the VU Medical Centre is offered to the patient. In agreement with their General Practitioner a decision will be made about further treatment or hospitalization.

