Although web-based administration of questionnaires is widely used, we should remind ourselves that the psychometric properties of internet-administered questionnaires may not be equal to those of paper-and-pencil versions [32]. On the other hand, in an earlier study we have found that the paper-and-pencil and the computerised versions of a short psychological well-being questionnaire appeared to be equivalent [33]. The major difference appears to be that respondents are more honest and revealing when filling out via the Internet, resulting in a relatively higher reported level of symptomatology. We have therefore chosen to confirm or decline the diagnosis of depression by a telephone administered diagnostic interview (CIDI). Our study will show if such diagnostic procedure is required in future projects applying W-CBT in order to reduce the risk of 'false positives'.

Also the psychometric properties of the following on-line questionnaires will be examined and compared to the paper-and-pencil versions: the PAID, SF-12 and the ADSCI.

We hypothesise that improved mood will be associated with improved diabetes self-management and we will test whether W-CBT has favourable effects on self-reported diabetes self-care behaviours, using the Amsterdam Diabetes Self-care Inventory (ADSCI) that was developed by our team and used in previous trials [12,13,34]. The psychometric properties of the Amsterdam Diabetes Self Care Inventory (ADSCI) have not yet been published, but a report on the validity and reliability of the scale is planned based on data on file.

Ethical and practical considerations have led us to decide that all participants are allowed to use additional mental health care (MHC) services during the trial. Usage of additional services therefore is a potential confounder that will be measured and taken into account in the statistical analyses.

Drop-out is often a problem in web-based therapy trials. In adapting the generic coping with depression course to the needs of people with diabetes, we expect to reduce drop-out. In an attempt to further reduce the attrition rate, support e-mails will be send out to participants by their coach, to encourage them to stay involved in the course. Likewise, those in the waiting list condition will receive e-mails aimed to maintain contact and encourage them to participate.

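### The post-test is tied to course completion in the intervention arm but to weeks 8 and 12 in the control arm; the two agree only for patients who finish on schedule

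*Protocol article*

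**What the plan says.** **Intervention arm.** Study Design places the measurements after baseline "directly after completing the web-based intervention, and at 1, 3, 4 and 6 months follow-up". Primary outcome measures fixes the CES-D "at baseline, directly after completion of the course and at one and six months follow-up". The Abstract and the Control group section use the same completion anchor. In Statistical Analyses, the responder rule (CES-D below 16) is also read after the course has been completed. Patients are told "to complete one session per week, during 8 consecutive weeks", with e-mail reminders.

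**Control arm.** Study Design gives controls "two additional measurements at 8 and 12 weeks after randomization" on top of the shared schedule. The Control group section says "After eight weeks they are invited per e-mail to fill in the questionnaires again", and that "they will start the course after 12 weeks". Weeks 8 and 12 are therefore the only measurements after baseline at which controls are still untreated.

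**Analysis and attrition.** Statistical Analyses promises intention to treat and compares the groups on CES-D by ANCOVA. GEE, chosen partly to limit loss from incomplete data, is assigned to the second analysis, a pre-post analysis of everyone who received the course. Power calculation anticipates 30% non-completion/exclusion and oversamples from 100 to 143 per arm. Strengths and Limitations says "Drop-out is often a problem in web-based therapy trials", and then describes support e-mails in both arms to limit it.

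**The concern.** In a randomised comparison, the time of measurement should not depend on what a patient does after randomisation. Here it does in one arm only. A patient who takes longer than eight weeks is measured later than the matching control and has had longer to recover without help. The 1-month visit inherits that delay, while the parallel control visit stays at week 12. A patient who stops after a few lessons never reaches the event that defines the post-test.

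If such patients are not measured, the between-group analysis sets intervention completers against all responding controls, which is not the intention-to-treat comparison promised. A post-test that was never collected cannot be recovered at the analysis stage.

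**Working it through.** **1. The plan's own figure.** Inputs from Power calculation: effect size 0.35, one-sided α = 0.05, power 80%, 100 per arm, 30% loss.
- n per arm = 2 × (1.645 + 0.842)² / 0.35² ≈ 100.9, so 101, against 100 stated. At 100 per arm the power is 79.7%.
- 100 / (1 − 0.30) = 142.9, so 143 per arm and 286 in total, as stated.

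The sample size is reproduced. If 100 intervention patients and all 143 controls are measured, one-sided power is 85.1%; with 100 and 100 it is 79.7%. The oversampling therefore already covers a 30% loss. What is at issue is bias, not power.

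**2. The two anchors side by side.**

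| Patient | Intervention post-test / 1-month visit | Untreated control measurement |
|---|---|---|
| On schedule (8 weekly lessons) | about week 8 / about week 12 | week 8 / week 12 |
| Finishes w weeks late | about week 8 + w / about week 12 + w | week 8 / week 12 |
| Does not finish | not defined in the text | week 8 / week 12 |

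**3. Timing, as an illustration.** Shift = mean delay (weeks) × spontaneous improvement (SD per week), assuming linear improvement. The documents give neither quantity; both ranges are assumptions.
- Low: 2 × 0.01 = 0.02 SD (0.02 / 0.35 = 6% of the target).
- High: 8 × 0.04 = 0.32 SD (0.32 / 0.35 = 91% of the target). This needs the arm to average 8 + 8 = 16 weeks on an eight-week course, so it is an outer limit.
- Completion at week 8: 0 × any rate = 0.
- If patients finish early on average, the sign reverses.

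**4. Missing non-completers, as an illustration.** Suppose a share p of the intervention arm has no post-test and would score g SD worse than completers, with the control mean unaffected. The full-arm mean is the completers' mean plus p × g, so the complete-case difference is shifted by p × g in favour of the course. Take p = 0.30, using the planned 30% as if it were all missing post-tests, and an assumed g of 0.1 to 0.5.
- 0.30 × 0.1 = 0.03 SD (9% of 0.35).
- 0.30 × 0.5 = 0.15 SD (43% of 0.35).
- If non-completers had stopped because they felt better, g would be negative and the shift would go against the course.

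**The case against.** The strongest reply is that the schedules were designed to match. The course is a moderated eight-week programme of consecutive weekly lessons with reminders and weekly coach feedback. Eight lessons end at about week 8 and one month later is about week 12, exactly when controls are measured. Measuring at the end of treatment against a time-matched waiting list is a legitimate choice. Figure 1, to which Study Design refers for the schedule, is not shown, and an article condenses a fuller protocol that may say when a patient who stops is sent the questionnaire.

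Much of this stands, and it rules out three stronger readings that a reader might infer:
- That the arms are compared at different times. As planned they are not; the times diverge only for patients off schedule, and no distribution of completion times is given. Nor do the documents call the course self-paced.
- That 43 intervention patients (0.30 × 143 = 42.9) will have no post-test. The 30% pools non-completion with exclusion, is applied to both arms and is not split. It is not a forecast of patients stopping lessons.
- That the bias favours the course. Nothing in the documents describes non-completers or their reasons for stopping.

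The reply does not remove the point. The completion anchor is not an omitted detail: it is stated repeatedly, including in the definition of the primary outcome and in the responder rule. Weekly lessons are an instruction to patients, not a fixed end date. The intention-to-treat statement does not supply a measurement time, and the GEE is assigned to the pre-post analysis rather than to the randomised comparison.

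**Conclusion.** The point holds as a measurement rule that is fixed badly. The intervention post-test and 1-month visit follow course completion, and the control comparison follows the calendar. They agree only for patients who keep the planned pace. Followed as written, the rule measures late finishers later than controls and gives non-completers no defined post-test, which sits poorly with the promised intention-to-treat analysis. It cannot be established that the full protocol or Figure 1 lacks such a time.

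Neither the size nor the direction of any bias follows from the documents. Under the stated assumptions, timing contributes between zero and about 0.3 SD, and missing non-completers 0.03–0.15 SD, against a design effect of 0.35. The correction should be made before data collection, because it is cheap and the missing measurements cannot be recreated later.

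**What to change.** - Send the post-test and 1-month questionnaires at 8 and 12 weeks after randomisation to every randomised patient in both arms, whatever the number of lessons completed.
- Define the between-group CES-D comparison and the rate of CES-D below 16 at those dates.
- Bring the wording in the Abstract, Study Design, Control group, Primary outcome measures and Statistical Analyses into line with each other and with Figure 1.
- Label follow-up after week 12 as uncontrolled, since controls are offered the course from then.

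The cost is a change to e-mail timing and visit definitions. The questionnaires are already online, and controls already receive a week-8 invitation. The sample size is unchanged. The one downside is that some slow patients will be measured before their last lesson.
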